## Abstract

**Introduction::**

Postmenopausal osteoporosis (PMOP), which is a common and frequently occurring age-related metabolic bone disease in perimenopausal women, severely affects patients living quality. Modern medicine therapies for PMOP have several problems such as side reactions, low compliance, and high costs. Thus, nonpharmacological modality is urgently needed. Although acupoint thread embedding treatment is widely used in clinical practice, there is no persuasive evidence of its effect on increasing bone mass for PMOP. This experiment aims to investigate the efficacy and safety of acupoint thread embedding on PMOP and elucidate the correlations among brain neural activation, bone mineral density (BMD), and clinical outcomes with magnetic resonance evidence, thus to explore its neural mechanism.

**Methods::**

This parallel designed, exploratory randomized, controlled, assessor-statistician-blinded, positive medicine clinical trial will include 70 participants with PMOP recruited from 2 traditional Chinese Medicine hospitals. These participants will be randomly allocated to a treatment group (Group Embedding) and a control group (Group Medication) in a 1:1 ratio. Participants in the treatment group will receive acupoint thread embedding treatment once 2 weeks in the following predefined acupoints: Shenshu (BL23), Sanyinjiao (SP6), Guanyuan (RN4), Ganshu (BL18), Dazhu (BL11), Xuanzhong (GB39), Zusanli (ST36), and Pishu (BL20). Meanwhile, the participants in the control group will take 0.3 mg Climen tablet orally, 1 tablet/day; every month has a schedule of the 21-day-continuous-taking-medicine period, and 7-day tablet-free period. There is a study period of 3 months and a follow-up period of 1 month for each group. The primary outcomes will be the following therapeutic indexed: Short-Form of McGill Pain Questionnaire (SF-MPQ), Osteoporosis Symptom Score during the observation period and follow-up period. The secondary outcomes will be Osteoporosis Quality of Life Scale (OQOLS), 16-item Assessment of Health-Related Quality of Life in Osteoporosis. In addition, functional magnetic resonance imaging (fMRI) scans and bone density test will be done before and after the observation period to show cranial neuroimaging changes. All the outcomes will be evaluated before and after treatment. The safety of interventions will be assessed at every visit.

**Discussion::**

We present study design and rationale to explore the effectiveness and neural mechanism of acupoint thread embedding for PMOP through these outcomes.

**Trial registration::**

Chinese Clinical Trial Registry, ChiCTR-INR-17011491.

## Introduction

1

The definition of postmenopausal osteoporosis (PMOP) is extremely reduced bone density after menopause.^[1]^ As the menopause period occurs younger nowadays, the PMOP also occurs more frequently. It is common in the population over 50 in China with a prevalence of 20.7% and has a high recurrence rate.^[2,3]^ PMOP patients would have several symptoms such as pain in waist and legs, limb weakness, hunchback, and easy fracture. Due to these symptoms, PMOP severely affects patients’ living quality, bringing a heavy financial burden on families and society.^[4]^ Postmenopausal women are the high-risk group of osteoporosis. They are at a special time when disease intervention is particularly important.

Modern medicine therapies and clinical medications are both efficacious in the treatment of PMOP. However, modern medicine therapies toward PMOP such as hormone replacement therapy (HRT), nonhormonal medication therapy have many flaws, such as the variety of side effects, high costs, cancer risk, drug dependence, and so on.^[5]^ Clinical medications toward PMOP such as bisphosphonates, calcitonins also have many flaws, such as renal damage risk, low compliance, the variety of side effects, high costs, and so on. From a clinical point of view, a strong need for effective, few side effects, low cost, and tolerable therapeutic treatments for PMOP still exists. Therefore, investigating the pathogenesis and seeking for valid curative measures are quite essential to postmenopausal patients.

Studies have reported that the etiology of PMOP is generally considered to be the decline in ovarian function and the decrease in estrogen levels in postmenopausal women. These will lead to hypothalamic-pituitary-ovarian axis dysfunction and affect bone metabolism. Some randomized controlled trial (RCT) studies have shown that acupoint thread embedding therapy (also called acupoint catgut embedding therapy and the name of the therapy changed due to the development of suture) can reduce the pain level of PMOP patients. It can also regulate hormone secretion levels, E2 level, reproductive endocrine, and bone metabolism of postmenopausal women.^[6–9]^ Until now, the exact mechanism of PMOP is still not clear.^[10]^

For traditional Chinese medicine (TCM), acupoint thread embedding treatment is widely used to treat a variety of health problems, including ostealgia from PMOP.^[11]^ However, there is no persuasive evidence of its effect on PMOP. Hence, some sensible evidence of its effectiveness and safety in treatment of PMOP is urgently needed. Imaging techniques can provide an effective approach to study the functional brain region. With the help of functional magnetic resonance imaging (fMRI), the changes in neural activity in different brain regions before and after the study can be gathered. Thus, the pathogenesis of PMOP may be revealed as well as the neural mechanism of acupoint thread embedding treatment.

## Methods/design

2

### Objectives

2.1

This study aims to investigate the efficacy and safety of acupoint thread embedding treatment on PMOP and explore its neural mechanism.

### Trial design and study setting

2.2

This study is a parallel designed, exploratory randomized, controlled, assessor-statistician-blinded, positive medicine clinical trial. Seventy participants with PMOP will be randomly assigned to the treatment group (taking acupoint thread embedding treatment, n = 35) and a control group (taking Climen treatment, n = 35) in a 1 : 1 ratio. The trial design and study flowchart are shown in Fig. 1.

**Figure 1 F1:**
[figure not shown]
Trial design and study flowchart.

### Recruitment

2.3

Two Chinese Medicine hospitals located in Guangdong, China, namely the Bao’an District TCM Hospital, the Affiliated Hospital of Guangzhou University of Chinese Medicine, and Guangdong Provincial Hospital of TCM, will recruit participants in the clinical practice setting. Clinical trial information will be posted on the bulletin board of each hospital and nearby communities, in WeChat subscription, in social software.

### Eligibility criteria: inclusion criteria

2.4

(1)Female subjects aged 45 to 70 years and have natural menopause for more than 2 years;(2)After the dual-energy X-ray absorptiometry, *T* value -2.5 ∼ -5.0 (L2-L4), and meet the diagnostic criteria of TCM syndrome;(3)Subjects voluntarily participated in the study and signed informed consent;(4)Subjects who can be able to cooperate and complete the fMRI scan.

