#### Study schedule

2.9.1

The study schedule is presented in Table 1. At the screening visit, participants will sign the informed consent form. In a baseline questionnaire, the following information will be obtained: age, occupation (physical/nonphysical), education level, last menstrual period, previous use of acupuncture, and expectation to acupoint thread embedding treatment. Moreover, Short-Form of McGill Pain Questionnaire (SF-MPQ), Osteoporosis Symptom Score, Osteoporosis Quality of Life Scale (OQOLS), 16-item Assessment of Health-Related Quality of Life in Osteoporosis (ECOS-16) must be completed at the baseline (week 0). Thereafter, study subjects will be randomized. There is a 3-month study period and a 1-month follow-up period for each group. In the study period, SF-MPQ, OQOLS, ECOS-16, and Osteoporosis Symptom Score will be evaluated every 4 weeks. fMRI and bone density test will be tested 2 times: in week 0 and week 12.

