#### Treatment group intervention

2.9.2

Acupoint thread embedding treatment will be applied to patients in the treatment group fortnightly, a total of 6 times during 3 months. Main acupoints are BL23, SP6, and RN4. If it is a liver-kidney deficiency case, BL18, GB39, BL11 will be added. If it is a kidney yang deficiency case, BL20, ST36 will be added. In each treatment, RN4 is a required acupoint. The rest acupoints can be used in the alternation of the left/right side. The location method is according to *Location of Acupoints* the National Standards of P.R promulgated by the State Bureau of Technology Supervision. The operating method follows the National Standards of P.R (GB/T 21709.10-2008) manipulations of acupuncture and moxibustion—Part 10 Acupoint catgut embedding. Details about the intervention group interventions and the acupoints location are described in the Standards for Reporting Interventions in Clinical Trials of Acupuncture (STRICTE) checklist in Tables 2 and 3.^[12]^

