### Outcome measure: primary outcomes

2.10

Outcomes will be evaluated using multiple indexes. The primary outcomes are measured by the following therapeutic indexes: Short-Form of McGill Pain Questionnaire (SF-MPQ), Osteoporosis Symptom Score during the observation period (3 months) and follow-up period (1 month). After baseline time, they will be tested at week 0, week 4, week 8 and week 12, and during the follow-up period.

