The study found several evidences about acupuncture (acupoint stimulation) treatment of PMOP^[9,15]^ and changes in bone mass caused by changes in brain endocrine hormones. Studies have shown that when the original bone resorption and bone formation balance is broken, after that, bone resorption increases, bone formation decreases, and osteoporosis is induced or aggravated.^[16,17]^ Bone physiology is coordinated by brain control and is associated with the transmission of leptin signaling.^[18]^ Hypothalamus release neurotransmitters via neuropeptides and monoamines, which regulate the secretion of gonadotropin-releasing hormone, growth hormone-releasing hormone, and thyrotropin-releasing hormone, interfering with bone growth and metabolism.^[19]^ Decreased expression of protein kinase C, bone morphogenetic protein, and its signal transduction molecule in osteoporosis model rats can significantly increase BMD.^[20,21]^ Acupoint embedding may regulate the neuroendocrine function by regulating the secretion of gonadotropin-releasing hormone (GnRH), growth hormone-releasing hormone (GHRH), and thyroid-stimulating hormone-releasing hormone (TRH) in the arcuate nucleus of the hypothalamus through monoamine neurotransmitters, then adjust the bone mass.^[19]^ Acupuncture (acupoint stimulation) can improve the symptoms of PMOP to some extent, and found that the brain's hormone levels have changed. Therefore, the researchers hypothesized that acupoint thread embedding therapy can improve the symptoms of PMOP and designed the study.

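### SF-MPQ pain is a primary outcome, but no entry criterion sets a minimum pain score, so women at zero at week 0 can enter and dilute the unadjusted comparison by an unknown amount

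*Protocol article*

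**What the plan says.** **Outcome.** Section 2.10 of the protocol article states: "The primary outcomes are measured by the following therapeutic indexes: Short-Form of McGill Pain Questionnaire (SF-MPQ), Osteoporosis Symptom Score". The Discussion gives the matching hypothesis: "the researchers hypothesized that acupoint thread embedding therapy can improve the symptoms of PMOP and designed the study".

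**Entry.** Section 2.4 selects women by age (45 to 70), natural menopause of more than 2 years, consent, ability to complete fMRI, and this disease criterion: "After the dual-energy X-ray absorptiometry, *T* value -2.5 ∼ -5.0 (L2-L4), and meet the diagnostic criteria of TCM syndrome". The ten exclusions in section 2.5 contain no pain or symptom threshold. Section 2.3 recruits through hospital and community notice boards and social media, so recruitment is not confined to women who present with pain.

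**TCM syndrome.** The article does not list the diagnostic items. Section 2.9.2 names two patterns, liver-kidney deficiency and kidney yang deficiency, only in order to choose acupoints, for example: "If it is a liver-kidney deficiency case, BL18, GB39, BL11 will be added".

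**Baseline.** Under section 2.9.1 the four scales, including the SF-MPQ, "must be completed at the baseline (week 0). Thereafter, study subjects will be randomized". The scores exist before allocation but do not decide entry.

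**Analysis.** Section 2.14 plans t tests, or rank tests where normality fails, between groups and before versus after treatment. It states no adjustment for baseline.

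**The concern.** The women are chosen mainly by bone density, while the primary endpoint measures pain. A woman with a qualifying T value and no pain sits at the bottom of the SF-MPQ. Her score can stay at zero or rise, but it cannot fall, whichever treatment she receives. Two things follow in the planned analysis:

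- She contributes no improvement in either arm, so the mean difference shrinks roughly in proportion to the share of such women.
- If post-treatment scores are compared, a cluster of zeros beside a spread of positive scores also inflates the variance within each arm.

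With 35 women per arm there is little room for either loss. A real difference in pain between embedding and Climen could be missed, and a null result could then be misread as the two treatments being alike. This is a mismatch between eligibility lists and a primary outcome that the article states, not a detail awaiting an analysis plan.

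**Working it through.** **No figure to reproduce.** The article gives 70 women, 35 per arm, two-sided testing at .05, and no effect size, SD or power. The following is an illustration.

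**Inputs from the article:** n = 35 per arm; two-sided alpha .05; unadjusted t test.

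**Assumed inputs:** share f at the floor, 10% to 40%; among women with pain, baseline mean 5 and SD 2 on a 0-10 score; before-after correlation 0.5; control fall 1.0; extra fall with embedding 0.68 × 2 = 1.36. Women at the floor score zero at both times in both arms.

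**Step 1: detectable effect.** d = (1.96 + 0.842) × √(2/35) = 0.67 SD for 80% power by the normal approximation; the t test needs about 0.68 SD.

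**Step 2: dilution.** With q = 1 − f, the mean difference in all women is 1.36q. The variance in an arm whose women with pain have mean μ and SD 2 is q(4 + μ²) − (qμ)². Power is approximately Φ(difference/SE − 1.96), with SE = √[(V₁ + V₂)/35].

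- *Post scores* (μ = 4.00 and 2.64), f = 20%: V = 5.76 and 4.32; SE = √(10.08/35) = 0.537; difference 0.8 × 1.36 = 1.088; ratio 2.03; power 53%.
- *Change scores* (SD of change = √(4 + 4 − 2 × 0.5 × 4) = 2; μ = 1.00 and 2.36), f = 20%: V = 3.36 and 4.09; SE = √(7.45/35) = 0.461; ratio 2.36; power 66%.

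Over f = 10/20/30/40% the formula gives 66/53/41/32% on post scores and 74/66/57/48% on change scores.

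**Step 3: simulation with the same inputs.** With nobody at the floor, power is about 79% (post) and 78% (change).

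| Assumed share at floor | t test, post, all women | t test, change, all women | t test, women with baseline pain | Baseline-adjusted, all women |
|---|---|---|---|---|
| 10% | 67% | 71% | 76% | 87% |
| 20% | 51% | 65% | 70% | 81% |
| 30% | 41% | 55% | 64% | 75% |
| 40% | 32% | 48% | 58% | 69% |

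The rank-sum fallback does not rescue the comparison: about 62/47/33/24% on post scores and 67/57/50/37% on change scores.

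**Step 4: cross-check by simple dilution.** Multiplying the effect of 0.67 by q with the SD unchanged gives 71/61/50/39%. Holding 80% would take 44/55/72/98 women per arm.

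**Step 5: what adjustment does.** With correlation 0.5 the residual SD is 2 × √0.75 = 1.73. With no floor, the ratio is 1.36/(1.73 × √(2/35)) = 3.29 and power about 91%. Adjustment therefore starts higher and still loses power as f grows. Its estimate remains an average over all women, including those who cannot improve. The undiluted effect comes from the subset with baseline pain.

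**The case against.** **The TCM criterion is itself an entry condition and may bring in symptoms.** This stands. A reader might infer that eligibility asks for no symptoms at all, and the article does not support that. Its diagnostic items may be in a fuller protocol. But the article nowhere says that either pattern requires pain, and the introduction's mention of waist and leg pain describes the disease rather than setting a rule.

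**The second primary outcome is not shown to be affected.** This also stands. The items of the Osteoporosis Symptom Score are not given, and it may overlap with the syndrome criteria.

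**The floor model is a worst case.** Partly right. Women near zero, as opposed to at zero, can still improve a little. A woman at zero can worsen, so preventing worsening could register. Holding floor women at zero throughout sets this aside.

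**The size is assumed.** Correct. Neither the share at the floor nor the pain distribution is in the article. A reader might infer that the trial is shown to be underpowered; it is not.

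**Restricting the primary analysis to women with pain would be a poor remedy.** This stands. On change scores restriction gains only a few points to about ten, while adjustment in all randomised women does better and discards nobody.

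**The trial is exploratory and also studies BMD and fMRI.** A population defined by DXA is defensible for those aims. It does not remove the mismatch with a pain endpoint, and the Discussion describes the purpose as verifying efficacy.

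**Conclusion.** The point holds for the SF-MPQ. Sections 2.4 and 2.5 let in women with a week-0 score of zero, these women cannot show improvement, and the unadjusted tests of section 2.14 count them at full weight. The direction of the loss is the same under every version of the planned test examined. Its size is not known: falls to 71-48% on change scores or 67-32% on post scores rest on an assumed 10-40% at the floor, an effect otherwise detectable with about 80% power, and the assumed pain distribution. If few women enter at zero, the loss is small. Nothing in the article establishes the same problem for the Osteoporosis Symptom Score. The change is worth making because the loss could be material with 35 per arm and the remedy is cheap.

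**What to change.** **Section 2.14.** Keep all randomised women in the primary SF-MPQ between-group comparison and adjust it for the week-0 score. Prespecify beside it the same comparison in women with a week-0 SF-MPQ above zero. The score is taken before randomisation, so this subset keeps the randomised comparison.

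**Section 2.4, for women still to be enrolled.** Require a week-0 SF-MPQ above zero, unless the TCM syndrome criteria already require pain. If they do, say so in the criterion.

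**Cost.** The analysis change is a few sentences and needs no new data. The subset result applies only to women with pain at entry and uses fewer participants. The entry criterion needs an amendment and may slow recruitment slightly. Recruitment began in September 2018, so early and late entrants would differ in eligibility; the baseline adjustment and the subset analysis help to address that.

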### Eligibility criteria: exclusion criteria

2.5

(1)Patients whose age is under 45 or over 70 years, natural menopause is fewer than 2 years;(2)Patients who have a history of hypersensitive reactions to acupoint thread embedding treatment or Climen;(3)Combined with other diseases affecting bone metabolism: endocrine diseases (gonads, adrenal glands, parathyroid glands, and thyroid diseases, etc), rheumatoid arthritis and other immune diseases, affecting the absorption and regulation of calcium and vitamin D, digestive tract and kidney diseases, malignant diseases such as multiple myeloma, long-term use of glucocorticoids or other drugs that affect bone metabolism, as well as a variety of congenital and acquired bone metabolism disorders;(4)Combined with malignant tumors, cardiovascular, cerebrovascular, liver, kidney, hematopoietic system, severe primary diseases, severe skin diseases, mental disorder patients;(5)Patients who have received osteoporosis medication (excluding calcium supplementation) within 6 months or have long-term use of drugs that may affect bone calcium metabolism;(6)Patients who have pathological changes in the brain, such as brain tumors;(7)Patients who have MR examination contraindications: such as aneurysm clips, implanted nerve stimulators, pacemakers, automatic defibrillators, cochlear implants (electrodes), or visual foreign bodies;(8)Patients who have a history of abuse of substances such as alcohol and drugs, or a history of dependence on alcohol or drugs;(9)Patients who are late disabled, deformed;(10)Ineligibility for the trial judged by the clinical trial investigator.

### Subject withdrawal criteria

2.6

(1)Violation of the inclusion criteria or fulfillment of the exclusion criteria;(2)Serious adverse events occurred during the treatment;(3)Withdrawal of consent by the subject or a legal representative;(4)Those who were unable to adhere to these treatments due to other medical conditions during the study period;(5)Violation of the clinical trial protocol by the investigator or the subject;(6)The loss to follow-up;(7)Use of medications or treatments that can affect the results of the clinical trial without permission from the investigator;(8)Inappropriate progress as judged by the investigator.

### Randomization and allocation concealment

2.7

The randomization number will be generated by PEMS 3.1 and made into random cards. The randomization number will be sealed in a predetermined randomization opaque envelope. The patients’ screening sequence numbers will be printed on the outside of the envelope, whereas the group names will be printed inside. The envelope containing an allocation sequence number for each patient will be opened right after each patient is verified to meet the eligibility criteria and has signed the written informed consent form. If any error or disclosure regarding randomization occurs, a new randomization sequence will be generated from the problematic serial number and applied to subsequent patients.

### Blinding

2.8

Considering the significant difference of treatment and the specificity of acupoint thread embedding treatment, double-blinding of the practitioners and participants is unfeasible. The assessor will be blinded. The treating physician will not assess the outcome measures. The assessor will be instructed to refrain from talking about the treatment in order to maintain blinding. The statistician and data collector will also be blinded. To guarantee the integrity of this trial, the study will strictly conduct randomization allocation and appoint different people to perform therapy, assessment, and statistical analysis according to the principle of blinding.

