Nevertheless, there are also limitations in this study. Concerning the unfeasible blinding to participants, one limitation is the possibility of a high risk of bias regarding blinding by unconcealed allocation. Therefore, we strictly conduct randomization and separate the acupuncturist, assessor, and statistician. Meanwhile, patients divided into the acupuncture intervention group may have more opportunities to make contact with their acupuncturists and establish a good doctor--patient relationship rather than those of the medicine control group, which is likely to improve the therapeutic effect. Hence, we will maintain close contact with patients in the control group by telephone, Internet, and so on to minimize this potential bias. At the same time, BMD is one of the important indicators of this study, but the change of BMD is not visible in the short term, which does not match the 3-month cycle of this study. However, as the main diagnostic index of PMOP, BMD cannot be ignored, so it remains in the experiment. To this end, researchers seek breakthroughs in neuroimaging, with a view to finding early imaging markers through fMRI before and after treatment, and judging the efficacy with other indicators such as symptom scale.

In conclusion, combining fMRI, BMD, and subjective symptom scale, the relevant outcomes are predicted to verify the efficacy and safety of acupoint thread embedding therapy. We believe that the results will exert a positive effect on acupoint thread embedding treatment for PMOP.

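### Assessor blinding and role separation are offered as the answer to unblinded participants but cannot act on patient reporting in the primary scales, and the named between-group tests ignore the baseline score

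*Protocol article*

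**What the plan says.** Section 2.8 (Blinding) states that "double-blinding of the practitioners and participants is unfeasible" and then sets out what is done instead: "The assessor will be blinded", and "The assessor will be instructed to refrain from talking about the treatment in order to maintain blinding". The statistician and data collector are also blinded, and different people carry out therapy, assessment and analysis.

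Section 2.10 names two primary outcomes, the SF-MPQ and the Osteoporosis Symptom Score. The conclusion of section 3 speaks of "combining fMRI, BMD, and subjective symptom scale", so the article itself treats the symptom scale as subjective.

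Section 3 discloses the weakness: "Concerning the unfeasible blinding to participants, one limitation is the possibility of a high risk of bias regarding blinding by unconcealed allocation". The next sentence gives the response: "Therefore, we strictly conduct randomization and separate the acupuncturist, assessor, and statistician". A further measure, extra contact with control participants, is aimed at unequal attention between the arms.

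Section 2.9.1 collects the baseline scores of all four scales before randomization. In the same baseline questionnaire it collects "previous use of acupuncture, and expectation to acupoint thread embedding treatment", and gives no purpose for these two items. Section 2.14 names a two-group t test, or a rank-sum test if the data are not normal, for between-arm comparisons of measurement data. It names no covariate.

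**The concern.** The safeguard does not match the bias it is meant to answer. A blinded assessor protects against an assessor who scores, prompts or interprets differently by arm. A blinded statistician protects against analytic choices made with knowledge of the arm. Neither acts on a participant who knows whether she received an embedding procedure or a tablet and whose own answers make up the score. The word with which section 3 links the admitted risk to the role separation presents the second as a remedy for the first, and it is not one.

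This matters because the subjective scales carry the efficacy conclusion. Section 3 accepts that BMD change does not show within a 3-month cycle, and says that efficacy will be judged with imaging and the symptom scales. A reader who takes the role separation as sufficient would read a difference on the primary scales as a treatment effect, when it could be partly or wholly an expectation effect.

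The second part concerns the analysis. The baseline score of each primary outcome is in hand before randomization, yet the between-arm tests named make no use of it as a covariate. In a trial of 70 women that gives up precision for no gain.

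**Working it through.** **1. Safeguards set against the bias.**

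| Measure in the article | What it limits | Acts on the patient's own answers? |
|---|---|---|
| Randomization (2.7, section 3) | Imbalance before treatment | No; the bias arises after she knows her arm |
| Blinded assessor who does not discuss treatment (2.8) | Prompting and scoring by arm | No, beyond limiting prompting |
| Blinded statistician and data collector (2.8) | Handling and analysis by arm | No |
| Extra contact with controls (section 3) | Unequal attention | No; she still knows her treatment |

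The limitation sentence in section 3 also attributes the risk to allocation that is not concealed, while section 2.7 describes concealment by sealed opaque envelopes. The problem is knowledge of treatment after allocation.

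**2. What a reporting bias would do.** The article gives 70 participants in a 1:1 ratio, so 70/2 = 35 per arm, with two-sided tests at 0.05. It gives no effect size, SD or power, so there is no stated figure to reproduce on this point. The size of any bias is not in the document, and a range of 0 to 0.5 SD in favour of embedding is assumed.

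Standard error of the between-arm difference: √(2/35) = 0.239 SD. The noncentrality for bias b is b × √(35/2) = 4.183b, for example 0.84 at b = 0.2 and 1.25 at b = 0.3. With 68 degrees of freedom, the chance of a significant result when there is no true difference is:

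| Assumed bias (SD) | 0 | 0.1 | 0.2 | 0.3 | 0.4 | 0.5 |
|---|---|---|---|---|---|---|
| Two-sided rejection | 5.0% | 7.0% | 13.1% | 23.6% | 37.8% | 54.1% |

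**3. Would adjusting for baseline expectation remove it?** No. In 4,000 simulated trials there was no true effect, a reporting bias of 0.3 SD, and an expectation score correlated 0.2 with outcome.

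| Analysis | Mean estimate | Significant |
|---|---|---|
| Unadjusted | 0.30 SD | 23% |
| Adjusted for expectation | 0.30 SD | 24% |

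Expectation is measured before randomization, so it is balanced between arms on average. The biased contrast is therefore unchanged.

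**4. How much could the arm-by-expectation interaction show?** With an assumed 50/50 split into high and low expectation there are 17.5 women per cell. The standard error of the interaction is √(4/17.5) = 0.478 SD. Power is about 18% for an interaction of 0.5 SD and 55% for 1.0 SD. For 80% power the interaction must be (1.960 + 0.842) × 0.478 = 1.34 SD. A bias that is the same at all expectation levels produces no interaction at all.

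**5. What adjusting for the baseline score does.** If r is the within-arm correlation between baseline and follow-up score, adjustment multiplies the variance of the between-arm difference by about 1 − r², compared with a test on follow-up scores. Compared with a test on change scores, whose variance factor is 2(1 − r), the ratio is (1 − r²)/[2(1 − r)] = (1 + r)/2. Both factors are at most 1, apart from one degree of freedom. The article gives no value of r, so the gain cannot be put as a single figure.

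**The case against.** The strongest reply is that the limitation is already disclosed. Section 3 speaks openly of a possible high risk of bias from unblinded participants, and section 2.8 does not claim that a blinded assessor removes patient-reporting bias. That stands, and it reduces this part to the unsupported step from the admitted risk to the remedy, and to what the reader is told to conclude.

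Three further points also stand. First, the article does not say who completes the Osteoporosis Symptom Score, so patient rating is an inference for that outcome. Second, a blinded assessor who does not discuss treatment still limits prompting and scoring influence, so the safeguard is not worthless for these scales. Third, the percentages rest on an assumed bias and would apply to any open-label comparison with 35 per arm; they are not evidence that the bias exists here.

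A reader might infer that expectation and previous acupuncture use were collected to probe this bias and then dropped. The document does not support that. Section 2.9.1 lists them beside age, occupation and education with no stated purpose, and further covariates or exploratory models may stand in a full protocol or analysis plan that is not shown. A reader might also infer that adjusting for them would bring the 13% to 24% back towards 5%. Steps 3 and 4 of the working show that it would not. Even a clear interaction could reflect genuine effect modification instead of bias.

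The baseline-score part survives these objections. The between-arm tests are named in section 2.14, so this is a choice the article states and not a detail it omits.

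**Conclusion.** The point holds in a limited form. Role separation and assessor blinding are presented as the response to unblinded participants, and they do not address reporting bias in the subjective primary outcomes. This is clear for the SF-MPQ and conditional on the unstated rater for the Osteoporosis Symptom Score. A difference on these scales cannot by itself be separated from an expectation effect, and the article should say so.

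The size of any bias is unknown. Under an assumed 0.2 to 0.3 SD, the error rate would be 13.1% to 23.6% at 35 per arm, and no analysis of the baseline variables changes that. The documents do not show that expectation data were collected for this purpose or wrongly left unused.

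Separately, section 2.14 names only unadjusted between-arm tests although baseline scores are available. Adjusting for the baseline score would gain precision by an amount that depends on a correlation the article does not give. It is an improvement in efficiency, not a remedy for the bias.

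**What to change.** **Sections 2.8 and 3.** State that blinding the assessor and statistician limits assessor and analyst influence but not patient-reporting bias. Add that a difference on the primary scales therefore cannot by itself be separated from an expectation effect. Remove the implication that role separation answers the lack of participant blinding, and attribute the risk to knowledge of treatment, not to allocation concealment. State who completes the Osteoporosis Symptom Score.

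**Section 2.14.** For each primary outcome, make the between-arm comparison a model with arm and the baseline value of that outcome, and say how clear departures from normality will be handled in that model. Baseline expectation and previous acupuncture use may be named as optional further covariates. If the arm-by-expectation interaction is reported, label it exploratory and low-powered, and state that it does not correct the bias.

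**Cost.** Some wording and a standard model. No new data and no extra participants are needed, because the baseline scores are already collected before randomization. The change should be fixed before the statistician learns the allocation.
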